## Abstract

Exercise training effectively mitigates aging-induced health and fitness impairments. Traditional training recommendations for the elderly focus separately on relevant physiological fitness domains, such as balance, flexibility, strength and endurance. Thus, a more holistic and functional training framework is needed. The proposed agility training concept integratively tackles spatial orientation, stop and go, balance and strength. The presented protocol aims at introducing a two-armed, one-year randomized controlled trial, evaluating the effects of this concept on neuromuscular, cardiovascular, cognitive and psychosocial health outcomes in healthy older adults. Eighty-five participants were enrolled in this ongoing trial. Seventy-nine participants completed baseline testing and were block-randomized to the agility training group or the inactive control group. All participants undergo pre- and post-testing with interim assessment after six months. The intervention group currently receives supervised, group-based agility training twice a week over one year, with progressively demanding perceptual, cognitive and physical exercises. Knee extension strength, reactive balance, dual task gait speed and the Agility Challenge for the Elderly (ACE) serve as primary endpoints and neuromuscular, cognitive, cardiovascular, and psychosocial meassures serve as surrogate secondary outcomes. Our protocol promotes a comprehensive exercise training concept for older adults, that might facilitate stakeholders in health and exercise to stimulate relevant health outcomes without relying on excessively time-consuming physical activity recommendations.

## 1. Introduction

The current report on the world’s aging population from the United Nations projected that, in 2050, nearly half of the world’s population will be living in countries with more than 20% of people aged 60 years and older [1]. Increasing life expectancy accelerates population aging [2], leading to considerable direct and indirect health care costs. Thus, healthy aging from individual and societal views has been entitled with “morbidity compression” [3] and includes multidisciplinary approaches with different physical, cognitive, social and psychological perspectives [4]. 

One strong precursor for successful aging is physical activity. Regular physical activity (approx. 150 min per week) can range from low exercise intensities to vigorous activities and can lead to notable risk reductions of non-communicable diseases and aging-associated diseases [5]. However, the adaptations to exercise training are usually very specific to the training modality and content [6]. In order to guarantee a broad range of training-induced adaptations in balance, strength, endurance, flexibility and cognition, exercise training recommendation should cover a variety of different multimodal tasks. Established exercise training guidelines for older adults are those of the World Health Organization [6] and of the American College of Sports Medicine [7]. Both associations independently recommend these physical training domains (i.e., aerobic exercise, resistance training, balance and flexibility training). Consequently, older adults are recommended to complete multiple training sessions of each domain. The total amount of these cumulative training sessions would result in seven weekly sessions. An expert panel additionally took into account the statements of the American Heart Association and published very similar recommendations [8]. This is a challenging and time-consuming physical activity guideline, which is particularly questionable, as “lack of time” is among the three most commonly mentioned burden for exercise participation in older adults [5]. Moreover, adherence rates for exercise training in older adults have been reported to decrease with every additional session per week [9]. 

Against this aforementioned background, Donath and colleagues [10] developed and proposed a multidimensional, functional and time-efficient agility training framework for older adults which has not been evaluated in a randomized controlled trial to date [10]. Their approach included changes of direction, start-stop movements, explosive and reactive strength and dynamic balance tasks. Agility training, therefore, comprises accelerations, decelerations, cutting maneuvers and different concentric and eccentric loads, combined with demanding spatial orientation tasks, strength and balance tasks in a very functional and integrative manner. Thereby, different levels of difficulty can be chosen for each exercise domain in terms of physical, perceptual, cardiovascular or cognitive demands. Overall, the agility training framework addresses all physical and selected cognitive health domains that are relevant throughout successful biological aging.

Agility is typically associated with sports games and usually comprises accelerations, decelerations, stop-and-go patterns, changes of direction (cutting maneuvers), and eccentric loads, combined with demanding spatial orientation tasks. When reviewing the scientific literature, very few studies have applied an agility-like training approach with older adults. The terminology “agility” is, more importantly, not present at all for this age group. However, relevant studies that performed group-based exercise training with older adults two to three times a week, comprising multimodal physical exercise training components and agility specific aspects like start-stop movements and cutting maneuvers, revealed meaningful improvements in strength [11,12,13], balance [14,15], cognitive [16] and endurance performance [12,14]. The greatest improvements were reported for functional mobility measures [12,13,17]. Thus, multimodal exercise training approaches have the potential to induce notable transfer effects to a variety of relevant physical exercise domains. However, those studies showed very heterogeneous training designs concerning the combination of training domains and the integration of agility-based training aspects. The first pilot study encompassing the agility approach for older adults, introduced by Donath et al. [10], includes an eight week-long agility program with high compliance (90 ± 8% of sessions) and notable improvements in endurance, balance and some strength measures [18]. This protocol of a randomized controlled trial was designed as a proof-of-concept training study that seems promising for a well-powered, long-term agility-based intervention study with different health-related surrogate measures.

In conclusion, it seems promising that agility training can serve as a feasible and time-efficient way to address a variety of health-related aspects relevant for the aging process. Numerous objective measures of neuromuscular, cardiovascular, cognitive and psychosocial origin can be challenged twice a week without excessive training volumes (which are not likely achievable by older adults). To our knowledge, no randomized controlled long-term intervention has applied the agility framework yet. Based on the above-mentioned rationales, we aim at introducing the protocol of an ongoing randomized controlled trial, investigating the effects of a one-year agility training intervention on neuromuscular performance, cardiovascular and cognitive functioning, as well as relevant psychosocial health outcomes in community-dwelling, healthy older adults. We specifically hypothesize that the agility training approach induces notable improvements in all physical performance measures (strength, balance, motor performance, aerobic capacity) after the one-year intervention period when compared to an inactive control group with at least moderate effect sizes that are comparable to other traditional training regimens. Secondly, we assume that those training effects will already be visible after six months of training with a further steady increase until the end of the one-year period. This study protocol was designed to contribute to a preventive multimodal training concept that can improve physical, cognitive and psychosocial health outcomes relevant to warrant healthy aging in an integrative and time-efficient way.

## 2. Materials and Methods 

### 2.1. Patient and Public Involvement

The study was designed without patient participation. After the end of the study, all participants will receive their individual results and the final publication. We intend to publish the results in a high-ranked, international journal. More importantly, we strive to produce a training app for coaches and therapists, which helps them to plan structured, progressive agility training sessions for elderly training groups.

### 2.2. Study Participants and Recruitment 

In the here-described ongoing one-year exercise training study, elderly participants, aged 60 years or older were recruited from the general population via a newspaper advertisement in Cologne (Germany). Older men and women were included if they were retired, community dwelling and independently living. They should not be engaged in more than two structured training sessions per week within three months before the start of the study. Their expected overall time of travel during the intervention period had to be less than two months. All participants had to accept randomization procedures to either the intervention or the control group. All participants needed to commute to the training site independently. Exclusion criteria were heavy smoking (“pack years” > 15), a body mass index (BMI) above 35 kg/m^2^ and a mini-mental state examination (MMSE) score below 26 [19]. Given contraindications for exercise training (any cardiovascular disease or depression without clearance from a medical doctor, chronic systemic inflammation or severe lung disease, insulin dependent diabetes, symptomatic cancer or acute cancer therapy, orthopedic diseases except those free of symptoms, more than mild, age-related osteoporotic changes) served as further exclusion criteria. Participants were informed about all inclusion and exclusion criteria prior to pre-testing. Additionally, they completed the “Physical Activity Readiness” questionnaire [20]. If they answered one or more questions with “Yes”, a medical consultation with their medical doctor was compulsory.

### 2.3. Experimental Design

The study is designed as a one-year two-armed, randomized, controlled intervention trial (Figure 1). All participants were requested to sign a written informed consent after being informed about all study procedures and after adequate time for consideration. Group assignment was conducted, applying the minimization method [21]. Accordingly, all participants were stratified to the intervention or the control group (intervention: control = 1:1). Sex, age, maximum knee extension strength, dual task gait speed and peak oxygen consumption (VO2peak) served as strata for balanced group allocation. Couples were stratified to the same group due to infrastructural, motivational and interference issues. The number of couples was evenly balanced in both groups. Group assignment was communicated to the participants after baseline assessment via telephone. Participants of the intervention group receive two weekly training sessions for one year. The control group does not receive any treatments. Only a brief written recommendation for physical activity is sent out. They will be given the opportunity to take part in a training program once a week after the end of the study for 6 months. Both groups are to keep a logbook on falls, diseases/injuries and exercise over the entire one-year study period.

Primary and secondary endpoints are collected at pre- and post-testing. An additional interim test with only a few measurements is provided after six months of training. At baseline (T1) and at the post-assessment (T3) after one year, all measurements are performed. This includes neuromuscular, cognitive, cardiovascular and psychosocial tests. At the interim assessment (T2), only selected neuromuscular and psychosocial measurements are assessed for reasons of time and reasonableness. 

T1 also includes a medical anamnesis and physical examination to rule out some severe exclusion criteria in addition to the medical clearance. At T1 and at T3, three lab visits on non-consecutive days, each lasting one to two hours, are required for each participant. On day one, cardiovascular, pulmonary and sonographic assessments are completed. On day two, neuromuscular, cognitive and psychosocial measurements are conducted. On the third day of assessment, the Agility Challenge for the Elderly (ACE) takes place. The interim assessments (T2) are completed within 45 min.

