### 2.8. Intervention

The first training session takes place immediately after group allocation. Participants train in three separate groups with a maximum of 13 participants in each group. Two trained study assistants supervise all sessions. Each of the training groups train twice a week for one year with a two-week Christmas break. Training sessions are held at gyms, located at the campus of the German Sport University Cologne. The gyms are equipped with regular basic equipment (e.g., mats, cones, ropes, hoops). The sessions last for 60 min in total and consist of a diverse 10 min agility-specific warm-up, followed by a 45 min agility training and a 5 min cool-down. Training is accompanied by music in line with the preferences of the participants. The warm-up either consists of a series of instructed exercises, dance-like routines or exercises incorporating balls. The agility training part is divided into three to four stations that the participants attend in pairs or in small groups. The load duration is one minute, followed by one minute of rest with four to five repetitions at each station. In the last third of the one-year intervention period, more complex parkour settings are installed. The individual load duration exceeds one minute and the time for rest is longer. As briefly described in the introduction, agility training includes four components: start-stop, change-of-direction, balance and strength. In order to progressively design training sessions, the one-year intervention period is divided into three thirds. During the first third, two of the four agility components are part of each training session, alternating every second session. In the second third, three of four components are combined in every session and then, only in the last third, all agility components are simultaneously integrated in each session. The complexity of the training sessions is progressively increased by changing the physical, perceptual and/or cognitive loads of the exercises. The training design and progression are displayed in Figure 2. Participants are always pointed to potential hazards during the exercises (e.g., stumbling over mats, slipping on a cone). They are taught to give each other assistance, e.g., during balancing exercises. Any adjustment of the original training protocol as well as adherence for every session is documented in detail by the coach. For each session, participants are asked to state their overall rate of perceived exertion (BORG scale) immediately after the end of the session. Additionally, in each session, three to four randomly chosen participants wear heart rate sensors (polar, H7, Buettelborn, Germany) to exemplarily capture heart rates during the training. A participant does not continue the allocated intervention if he or she requests it or suffers pain or an injury. Adverse events are recorded and potential sources will be discussed and eliminated if necessary.

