
### 2.9. Sample Size Estimation and Statistical Procedures

A sample size estimation was conducted with G*Power (Version 3.1, Heinrich Heine University, Duesseldorf, Germany). 68 participants (34 per group) are needed for statistical analysis, assuming moderate effects (f = 0.2) for training-induced changes in the primary outcomes (statistical power 90%, two-sided significance level α=.05). Expecting a realistic dropout rate of about 25%, a total of 85 participants were initially recruited.

Data entry will be double-checked and data ranges will be controlled for plausibility. Two researchers ([name]) will do data management and analysis. Independently conducted two-factorial repeated measured analyses of co-variance (rANOVA), with the respective endpoint as a baseline measure serving as the covariate [53], will be computed as primary analysis to assess the time course of adaptations between groups (factor 1: control group vs. intervention group; factor 2: time point of measurement; baseline, interim, post). The rANOVA interaction term between both factors is the main term of interest. Together with 90% confidence intervals, change scores from T1 to T3 and from T1 to T2 and T2 to T3 are calculated to arrive at an estimate of the size of the observed effects. The intention-to-treat analysis will be computed. The intention-to-treat analysis will be compared to as-treated analysis. Potential differences will be discussed.

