### 3.3. Potential Limitations and Risk for Bias

Participants were recruited from the general population via newspaper advertisement, which could lead to a selective recruitment of those older adults, that are intrinsically motivated to exercise and wo are already physically active. Group allocation was done according to the minimization method, which is comparable to a randomization method in smaller samples [21]. It allows us to balance important demographic measures and primary and secondary outcomes with possibly small group differences at baseline. Sex, age, maximum knee extension strength, dual task gait speed and VO2peak serve as strata for minimization, notably attenuating the risk of bias. Only participants who stated that they were willing to be randomized in one of the two groups could take part in the study to minimize dropout in the control group. Group preferences were strictly not allowed. Couples were randomized to the same groups. As is usual in exercise intervention studies, the blinding of participants is not possible. Due to personal and financial resources, the blinding of assessors and coaches is not possible either, which yields an acceptable risk for bias. Measurements are standardized and performed in the same room by the same assessor at T1, T2 and T3. Measurements are scheduled at the same time of the day for T1, T2 and T3 if possible. For each measurement domain, one gold-standard setter teaches all other assessors. The control group does not receive any treatments, but for ethical reasons they receive written recommendations for physical activity. Their potential autonomous exercise over the one-year period could influence the results of the study and is, therefore, captured via a logbook.

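### The primary model does not reflect the allocation: most minimisation factors and the pairing of couples are left out, with a modest net effect of unknown sign, and the abstract names a different allocation method

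*Protocol article*

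**What the plan says.** **Allocation.** Section 2.3 states: "Group assignment was conducted, applying the minimization method [21]". It names the balancing factors: "Sex, age, maximum knee extension strength, dual task gait speed and peak oxygen consumption (VO2peak) served as strata for balanced group allocation". Section 3.3 repeats both the method and the five factors. The abstract says otherwise: "Seventy-nine participants completed baseline testing and were block-randomized to the agility training group or the inactive control group".

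**Couples.** Section 2.3: "Couples were stratified to the same group due to infrastructural, motivational and interference issues", and "The number of couples was evenly balanced in both groups". The number of couples is not given.

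**Primary model.** Section 2.9 sets one repeated-measures analysis of covariance per endpoint, group by time, "with the respective endpoint as a baseline measure serving as the covariate". The interaction is the term of main interest. No other covariate and no couple term is named.

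**Primary endpoints.** There are four: knee extension strength, reactive balance, dual task gait speed and the ACE. The first and third are also minimisation factors.

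**The concern.** Minimisation and joint allocation of couples both change the sampling variance of the group difference. An analysis that ignores them does not estimate that variance correctly.

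- **Balanced factors left out.** If a factor predicts outcome and the arms were forced to be alike on it, the true variance of the group difference falls. The model still counts the factor's contribution as residual noise. The standard error is too large, the test is conservative, and precision is lost.
- **Couples treated as independent.** Partners in the same arm who respond alike carry less information than two unrelated people. The standard error is too small and the test is anti-conservative.

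At stake is whether the p-values and intervals for the primary endpoints have their stated error rates, and whether baseline data already collected are used. The mismatch in naming matters too: block randomisation and minimisation call for different analyses, and a reader of the abstract would expect the wrong one.

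**Working it through.** **1. Which factors enter which model (Sections 2.3, 2.5, 2.9)**

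| Primary endpoint | In the model through own baseline | Minimisation factors absent |
|---|---|---|
| Knee extension strength | knee extension strength | sex, age, gait speed, VO2peak |
| Dual task gait speed | dual task gait speed | sex, age, knee strength, VO2peak |
| Reactive balance | none of the five | all five |
| ACE | none of the five | all five |

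**2. The plan's own figure.** Section 2.9 gives f = 0.2, power 90%, two-sided alpha 0.05 and N = 68. For a within-between interaction, λ = f²·N·m/(1−ρ). Two time points (m = 2) and ρ = 0.5 are assumptions; the article gives neither. Then λ = 0.04 × 68 × 2/0.5 = 10.88 on 1 and 66 degrees of freedom, and power is 0.9015. The 68 reproduces, with every participant counted as independent.

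**3. Omitted factors alone.** Let R² be the share of variance in the tested contrast that the omitted factors explain beyond own baseline (assumed). With perfect balance, true variance/model variance = 1 − R², and type I error = 2[1 − Φ(1.96/√(1−R²))]. For a design with 90% nominal power, power is Φ(1.2816/√(1−R²)) without adjustment and Φ(3.2415/√(1−R²) − 1.96) with it.

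| R² | Model SE too large by | Type I error | Power, unadjusted → adjusted |
|---|---|---|---|
| 0.10 | 5.4% | 3.9% | 0.912 → 0.927 |
| 0.20 | 11.8% | 2.8% | 0.924 → 0.952 |

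The gain in power is 1.5 to 2.8 points. At R² = 0.05 and 0.30 the type I error is 4.4% and 1.9%.

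**4. Couples alone.** Let q be the share of participants in couples and ICC the within-couple correlation of the analysed contrast (both assumed). Variance factor = 1 + q·ICC.

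| q | ICC | Variance factor | Type I error | Power at N = 68 |
|---|---|---|---|---|
| 0.1 | 0.05 | 1.005 | 5.1% | 90.0% |
| 0.3 | 0.3 | 1.09 | 6.1% | 87.5% |
| 0.5 | 0.5 | 1.25 | 8.0% | 82.5% |

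**5. Both together.** True variance/model variance ≈ (1 − R²) + q·ICC.

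| R² | q | ICC | Ratio | Type I error |
|---|---|---|---|---|
| 0.20 | 0.1 | 0.1 | 0.81 | 2.9% |
| 0.10 | 0.3 | 0.3 | 0.99 | 4.9% |
| 0 | 0.5 | 0.3 | 1.15 | 6.8% |

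**6. Simulation check.** Minimisation with N = 79 and couples moved as a unit; single follow-up ANCOVA; own baseline is itself one of the five factors and each of the other four is worth 0.3 residual SD. There were 2,000 runs, with Monte Carlo error of about 0.5 points.

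| Couples, ICC | Covariates | Mean model SE | True SE | Type I error |
|---|---|---|---|---|
| none | own baseline | 0.263 | 0.241 | 3.1% |
| none | all five | 0.227 | 0.225 | 4.6% |
| 16, 0.3 | own baseline | 0.262 | 0.256 | 4.5% |
| 16, 0.3 | all five, couples ignored | 0.227 | 0.240 | 6.4% |

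Adding the factors while still ignoring couples removes the offset: type I error moves from 4.5% to 6.4%.

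**7. The step 3 figures are upper limits.** The first two rows of the simulation imply R² ≈ 1 − (0.227/0.263)² = 0.255. Perfect balance would then give a type I error of about 2.3%; the simulation gave 3.1%, because minimisation on five factors in 79 people balances only approximately.

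**The case against.** **The errors may cancel.** They have opposite signs, and one plausible combination gives 4.9%. This stands as a limit on the claim. It is no reason to leave the model as it is: the offset depends on quantities the article does not report and will differ between the four endpoints.

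**A reader might infer that all five factors are missing everywhere.** The article does not support that. Knee extension strength and dual task gait speed each enter one model as own baseline.

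**A reader might infer that the p-values are known to be wrong in a given direction.** They are not. No document value fixes R², the number of couples or the within-couple correlation.

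**Simply adding covariates would not help.** This stands. The tested term is group by time. With complete data, a covariate entered only as a main effect, or a couple random intercept, shifts all time points equally and drops out of that contrast.

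**The training groups.** Section 2.8 says: "Participants train in three separate groups with a maximum of 13 participants in each group". A reader might count this as a further allocation fault. It is not one: it concerns delivery in one arm. Sizing it needs an assumed correlation, 13 is a maximum (34 analysed in three groups is about 11 each), and a random effect with three levels is barely estimable. A sensitivity analysis is optional at most.

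**The analysis plan is not shown.** This does not remove the point, because Section 2.9 fixes the primary model and its covariate.

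**Conclusion.** The point holds in a limited form. Three things are certain from the text:

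- Sex, age and VO2peak are absent from all four primary models, and all five minimisation factors are absent for reactive balance and the ACE.
- Couples were allocated as a unit and the stated model has no term for them.
- The abstract contradicts Sections 2.3 and 3.3 on the allocation method.

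The statistical effect is modest and its sign is unknown. With R² from 0 to 0.20 and q·ICC from 0.01 to 0.15, the type I error is about 3% to 7%. Adjustment gains about 1.5 to 3 points of power at R² of 0.10 to 0.20, and that assumes perfect balance. All these inputs are assumptions. The naming mismatch changes no analysis if Section 2.3 is right. The change is worth making because it uses data already collected and removes an error that nobody can size from the article.

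**What to change.** 1. In every primary model, add the baseline values of the five minimisation factors, without entering the endpoint's own baseline twice. That means four extra covariates for knee extension strength and dual task gait speed, and five for reactive balance and the ACE.
2. Cross these covariates with time so that they act on the group-by-time contrast. Alternatively, estimate the group difference at T3 by ANCOVA with these covariates. That suits the ACE in particular, which Section 2.7 does not list at the interim assessment.
3. In the same step, use couple-clustered standard errors or a couple effect that acts on change. Do not make step 1 without this one.
4. Report the number of couples in each arm.
5. Reconcile the abstract's allocation method with Sections 2.3 and 3.3.

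The cost is four or five degrees of freedom (per time contrast where covariates are crossed with time), and a mixed model or clustered standard errors in place of a plain rANOVA. That is more than a change of wording, but no new data are needed.

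### Couples were allocated as pairs, but the primary analysis and sample size treat all participants as independently allocated; if partners' changes correlate positively, standard errors are somewhat too small

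*Protocol article*

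**What the plan says.** Section 2.3 (Experimental Design) describes 1:1 allocation by minimization and adds: "Couples were stratified to the same group due to infrastructural, motivational and interference issues". It continues: "The number of couples was evenly balanced in both groups". Couples are therefore present in both arms. Section 3.3 (Potential Limitations and Risk for Bias) repeats the point, "Couples were randomized to the same groups", and draws no consequence for the analysis.

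Section 2.9 (Sample Size Estimation and Statistical Procedures) sets the primary analysis: "Independently conducted two-factorial repeated measured analyses of co-variance (rANOVA), with the respective endpoint as a baseline measure serving as the covariate". The factors are group and time point, and "The rANOVA interaction term between both factors is the main term of interest". Effect sizes are to be reported as follows: "Together with 90% confidence intervals, change scores from T1 to T3 and from T1 to T2 and T2 to T3 are calculated". The sample size is 68 people, 34 per group, for f = 0.2, 90% power and a two-sided 5% level. Section 2.9 mentions no couple term, clustered variance or design effect. The article does not give the number of couples or a within-couple correlation.

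**The concern.** When two people are allocated together, the analysis should allow for the two results not being independent. If partners tend to improve or decline together, a pair carries less information about the group difference than two unrelated people. An analysis that counts them as two independent people then understates the variance. P-values become too small, the 90% intervals cover less than 90%, and the effective sample size falls below the head count.

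Balancing the number of couples between arms does not prevent this: it equalizes how many pairs each arm holds but leaves the correlation within a pair. A term for training class would not deal with it either, since control couples attend no class.

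This is more than a detail left to an analysis plan. The article states both the allocation rule and the main parts of the primary model, and the two do not match.

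**Working it through.** **Inputs from the article.** 79 randomized (Abstract); 68 needed for analysis, f = 0.2, power 90%, two-sided alpha 0.05 (section 2.9); couples kept together and balanced across arms (section 2.3).

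**Inputs that must be assumed.** Number of couples k: 6 to 20 among 79. Within-couple correlation of baseline-adjusted change, rho: 0.1 to 0.3, with -0.1 as a sensitivity value.

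**Step 1: reproduce the stated sample size.** For the within-between interaction of a repeated-measures ANOVA, the noncentrality is lambda = f² × N × m / (1 − r), where m is the number of time points and r the correlation between them. With m = 2 and r = 0.5, neither of which is stated, lambda at N = 68 is 0.04 × 68 × 2 / 0.5 = 10.88. Power is then 0.9015, and 68 is the smallest even N that reaches 90%. (With m = 3 and r = 0.5 it would be 56.) So 68 is reproduced as a count of independent individuals with no design effect.

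**Step 2: design effect.** With cluster sizes of 2 for couples and 1 for singles,

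DEFF = 1 + rho × (Σm² / Σm − 1), where m is now cluster size.

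- 6 couples, 67 singles: Σm² = 6 × 4 + 67 = 91; 91/79 = 1.152; at rho = 0.1, DEFF = 1 + 0.1 × 0.152 = 1.015.
- 20 couples, 39 singles: Σm² = 20 × 4 + 39 = 119; 119/79 = 1.506; at rho = 0.3, DEFF = 1 + 0.3 × 0.506 = 1.152.

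**Step 3: consequences if the pairing is ignored.**

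| | 6 couples, rho 0.1 | 20 couples, rho 0.3 |
|---|---|---|
| DEFF | 1.015 | 1.152 |
| True SE / naive SE (√DEFF) | 1.008 | 1.073 |
| Naive SE too small by (1 − 1/√DEFF) | about 1% | about 7% |
| Effective size (79/DEFF) | about 78 | about 69 |
| Real error of nominal 5% test, normal approximation | 5.2% | 6.8% |
| Same, simulated (arms of 39 and 40, t-test, 40,000 runs) | 5.1% | 7.0% |
| Coverage of nominal 90% interval | 89.7% | 87.5% |

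The normal-approximation and simulated error rates differ by no more than simulation noise would explain. Intermediate simulated cases are 5.8% (10 couples, rho 0.3) and 6.1% (14 couples, rho 0.3).

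**Step 4: power.** Dividing lambda by DEFF, power at N = 68 falls from 90% to about 89.7% at DEFF 1.015 and about 85.8% at DEFF 1.15. The numbers needed for 90% power become 70 and 78.

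**Step 5: sign.** With 30% of participants in couples and rho = −0.1, DEFF = 1 − 0.3 × 0.1 = 0.97. The true standard error is 0.985 times the naive one, and the error rate is about 4.7%. The test is then slightly conservative.

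**Step 6: which correlation counts.** The interaction and the change scores are within-person contrasts, so stable similarity between partners cancels. In a simulation with 10 couples per arm, partner correlation 0.5 in level and none in change, the unadjusted test on change had an error rate of 4.9% (20,000 runs). Only correlated change matters.

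The same reasoning rules out one remedy. With 40 per arm, 10 couples per arm and partner correlation 0.3 in both level and change, the mean standard error of the interaction was 0.219 both without and with a time-constant couple intercept. The actual standard deviation of the estimate was about 0.24 (only 60 runs, so imprecise).

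**The case against.** The strongest case against has four parts.

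- **Direction.** The article does not show that partners' changes are correlated. Its reasons for joint allocation, "infrastructural, motivational and interference issues", can be read as logistics and avoidance of contamination between arms. Shared household and age are mostly stable traits and largely drop out. This stands: the direction is conditional.
- **Net effect.** Sex, age and VO2peak were balancing factors in the minimization but are not covariates in the stated model. Leaving out prognostic balancing factors tends to make tests conservative, which works the other way. This also stands as a limit on the net direction, but it is a separate matter and does not correct for pairing.
- **Size.** At the low end the effect is negligible. The upper end requires 40 of 79 people (51%) to have enrolled as couples, which newspaper recruitment neither supports nor excludes. This stands.
- **Scope.** A short statistical section may leave the error structure to an analysis plan. This has some force, but the section gives factors, covariate, term of interest and sample size, and none of these reflects the stated allocation by pairs.

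A reader might infer three stronger things that the article does not support. One is that the error bars are definitely too narrow; without the number of couples or the correlation, that cannot be said. Another is that partners share training class, attendance and dropout; the article describes three training groups but does not say partners train together. The last is that the plan itself asserts independence between partners, from "Independently conducted two-factorial repeated measured analyses of co-variance (rANOVA". There the word most naturally means separate analyses for each endpoint.

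**Conclusion.** The mismatch is real and the likely effect is modest. Couples were allocated as pairs in both arms, while the primary analysis and sample size make no allowance for this. Whether the intervals are too narrow depends on positive correlation between partners' changes, which is plausible but not documented. Under the assumed ranges (6 to 20 couples, correlation 0.1 to 0.3), standard errors are about 1% to 7% too small, the nominal 5% test has a real error rate of about 5.1% to 7.0%, and 79 people carry the information of about 69 to 78. These figures isolate the effect of pairing and do not net it against anything else in the design. They do not show that any conclusion of the trial would change. The point should be corrected because doing so needs no new data.

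**What to change.** In section 2.9, state that the couple is the allocation unit for participants who enrolled together. Compute standard errors and confidence intervals for the group-by-time effect and the change scores with clustering on couple, singles as clusters of one, and a small-sample correction, since the number of couples may be low.

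A random-effects version is acceptable if the couple effect acts on the baseline-adjusted follow-up or the change (a couple-by-time effect). A couple intercept constant over time should not be used as the remedy, because it cancels from the interaction. Any permutation or bootstrap check should move couples as whole units.

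Report the number of couples per arm so that readers can judge the size of the issue.

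The cost is small: couple membership is known from allocation, and only the variance calculation changes. Intervals may widen slightly.
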